***Immuno-genetics***

An additional aspect to be assessed in this study is the impact of genetic factors influencing the response to immunisation. Host immuno-genetics are likely to play a critical role in modulating the responses to paediatric vaccines. Twin studies on several vaccines including measles, mumps and rubella, have shown high heritability of vaccine antibody responses29. Some genetic associations have already been identified between genes of the adaptive and innate immune response and some vaccines, for example human leukocyte antigen (HLA) alleles and measles antibody responses30,31, and IL-1β polymorphisms and hepatitis B vaccine responses32. These studies have been small scale and based on single candidate genes and the extent to which genetic variation contributes to vaccine responses remains poorly understood. Insight into which genetic variants affect responses to specific vaccines will be of value for 2 main reasons:

1. it will help identify the critical immune pathways leading to protection after vaccination and lead to the production of more effective vaccines
2. it will help identify genes that may play important roles in wild-type infection and lead to better understanding of disease pathogenesis, which in turn may lead to the development of novel therapies

The blood samples obtained in this study provide an opportunity to extract DNA from the cellular plug remaining after serum centrifugation. The DNA samples obtained in this study can then contribute to a DNA bank pooling samples from multiple different Oxford Vaccine Group studies. These DNA samples can then be used for genome wide analysis of the genetic factors influencing the host response to the vaccines received in the relevant studies. This DNA extraction and storage will only occur with the specific consent of participants, and DNA will not be analysed for any other purpose than to assess factors influencing the immune response to vaccines.

# OBJECTIVES

The overall objective of this study is to determine the relative immunogenicity of different schedules of serogroup C meningococcal (MenC) vaccine in the first year of life and to determine whether a reduced dose schedule could be used to save costs for the NHS.

## 5.1 Primary Objective

## The primary objective of this study is to demonstrate non-inferiority of the geometric mean titres (GMTs) of meningococcal serogroup C (MenC) specific serum bactericidal antibodies, using rabbit complement (rSBA), 1 month after a 12 month dose of Hib-MenC vaccine in children receiving a single dose of MenC-CRM197vaccine at 3 months of age (Single Dose priming) compared with those receiving 2 doses at 3 and 4 months of age (Two Dose priming). Non-inferiority of the MenC serum bactericidal antibody geometric mean titres (SBA GMTs) would imply that the reduced schedule of MenC immunisation would be a more cost effective method of providing sustained immunity against MenC disease through childhood.

## 5.2 Secondary Objectives

Reduced dose MenC component:

1. To assess whether MenC SBA GMTs measured 1 month after a 12 month dose of Hib-MenC are higher in children previously receiving Single Dose MenC-CRM197 vaccine priming at 3 months of age (Single Dose MenC-CRM197 Group) than in those receiving no priming doses of MenC vaccine (Control Group), demonstrating whether single dose MenC priming offers any advantage over no priming in terms of antibody levels at 13 months, and whether a single infant dose of MenC vaccine induces immune memory.

2. In an exploratory analysis, to compare the MenC SBA GMTs at day 6 after the 12 month dose of vaccine in a subset of participants (64 participants each from the Single Dose MenC-CRM CRM197, Single Dose MenC-TT and Two Dose MenC Groups, and all 64 in the control group: n=256) from all four groups, as it has been proposed that assessment of specific antibody levels at this earlier time point will more effectively discriminate between 'primed' and 'unprimed' immune responses to vaccines.

3. To assess the MenC SBA GMTs 2 months after a dose of MenC-CRM197 vaccine at 3 months of age (Single Dose MenC-CRM CRM197 Group) compared to the MenC SBA GMTs taken 1 month after a course of MenC-CRM197 vaccine at 3 and 4 months of age (Two Dose MenC Group), and to a Control Group receiving no infant MenC immunisation who would be sampled at 5 months of age.

4. To assess MenC SBA GMTs 2 months after a dose of a MenC-TT vaccine at 3 months of age (Single Dose MenC-TT Group) compared to a Single Dose of a MenC-CRM197 conjugate vaccine (Single Dose MenC-CRM197 Group), and to the Control Group, on a blood sample taken at 5 months of age.

5. To assess MenC SBA GMTs measured 12 months after a 12 month dose of Hib-MenC in all groups receiving priming vaccines with MenC-CRM197, or no priming, to determine whether 2 dose MenC priming offers any advantage over single dose MenC priming or no priming in terms of antibody levels at 24 months.

6. To assess MenC SBA GMTs 12 months after a 12 month dose of Hib-MenC in children previously receiving a single dose of a MenC-TT vaccine at 3 months of age (Single Dose MenC-TT Group) compared to a single dose of a MenC-CRM197 conjugate vaccine (Single Dose MenC-CRM197 Group).

7. It is intended to measure the numbers of MenC specific memory B cells in the blood at 5 months, 12 months, 6 days following the 12 month booster dose, at 13 months and 24 months on a subset of participants. Specific memory B cells against diphtheria and tetanus will also be measured and used as a control. As many participants as possible would be included in this subset but the number would be determined by the practicalities of getting the blood to the laboratory in time (before midday) for processing.

8. To assess the local and systemic adverse reactions experienced by participants in the four different study groups after immunisation with each dose of the MenC-CRM197, MenC-TT and Hib-MenC vaccines.

Alternating limb component

1. To compare the *S. pneumonia*e IgG GMCs and percentage of infants with serum concentration of *S. pneumonia*e specific IgG ≥0.35 g/ml for all 13 PCV13 serotypes at 5, 12, 13 and 24 months of age in children receiving PCV13 in a consistent limb (subgroups ‘a’) vs those receiving this in alternating limbs (subgroups ‘b’).
2. To compare serotype specific pneumococcal B cell phenotype in a subset of participants at 5, 12, 13 and 24 months of age in children receiving PCV13 in a consistent limb (sub groups ‘a’) vs those receiving this in alternating limbs (subgroups ‘b’).

3. To compare the anti-PRP IgG GMCs and percentage of infants with serum concentration of anti-PRP IgG ≥0.15g/ml and ≥1.0 g/ml and at 5, 12, 13 and 24 months of age in children receiving DTaP-IPV-Hib in a consistent limb (sub groups ‘a’) vs those receiving this in alternating limbs (subgroups ‘b’).

4. To compare the anti-tetanus toxoid GMCs and percentage of infants with anti-tetanus toxoid >0.1 IU/ml at 5,12, 13 and 24 months of age in children receiving DTaP-IPV-Hib in a consistent limb (sub groups ‘a’) vs those receiving this in alternating limbs (subgroups ‘b’)

5. To compare the local or systemic vaccine reactions in subgroups a and b at each vaccination time point.

**6. TRIAL DESIGN**

6.1 Summary of Trial Design

This is a phase IV open label randomised controlled trial enrolling 498 participants. Study participation would be for 23-24 months during which there will be 8 study visits as outlined in the attached figure and as detailed in section 6.4.2. A list of the study procedures and the interval between study visits are shown in Appendices A, B and C. Study visit 6 would be performed in all participants in the control group, and an equal number (i.e. 64) of participants in the Two Dose MenC, Single Dose MenC-CRM197 and Single Dose MenC-TT groups (as determined by randomisation at enrolment).

***Two dose MenC Group** **n=160**

MenC-CRM197 at 3 & 4 months

Visit 4

Visit 1

***Single dose MenC-CRM197 Group n=160**

MenC-CRM197 at 3 months

Visit 5

Visit 6**

Visit 7

Hib-MenC boost + PCV13 at 12 months

VP

VP

VP

VP

*Control group n=64

Visit 2

Visit 3

MMR

Visit 8

VP

*Single dose MenC-TT Group n=114 MenC-TT at 3 months

*Participants would be randomised to receive MenC-CRM197 at 3 and 4 months (Two Dose MenC Group), or a single dose at 3 months (Single Dose MenC-CRM197 Group) or a single dose of MenC-TT at 3 months (Single dose MenC-TT Group) or no priming doses (Control Group). All participants will receive the DTaP-IPV-Hib vaccine at 2, 3 and 4 months and the PCV13 at 2 and 4 months according to the UK immunisation schedule. All participants would be boosted with the Hib-MenC vaccine and the booster dose of PCV13 at 12 months and will receive the MMR vaccine at 13 months.

Venepuncture (VP), taking 5 ml of blood, will be performed at 5 months (Visit 4), and taking 7.5ml of blood will be performed at 12 months (Visit 5), 12 months+6 days (Visit 6), at 13 months (Visit 7) and at 24 months (Visit 8). Two attempts may be made to obtain a blood sample at each visit, if the parent gives verbal consent at the time of the procedure for a second attempt. If no blood is obtained, a second visit may be made if the parent agrees to this.

** Visit 6 will be performed on all participants in the control group and a subset of 64 participants in the Two Dose MenC, Single Dose MenC-CRM197 and Single Dose MenC-TT groups (as determined by randomisation at enrolment, see section 6.4.4)

In addition, participants will be randomised at enrolment to receive PCV13 and DTaP-IPV-Hib in either consistent limbs (subgroup a) or alternating limbs (subgroup b) as follows

| **Subgroup a**  (Consistent limbs) | **Subgroup b**  (Alternating limbs) |
| --- | --- |
| DTaP-IPV-Hib in right leg at 2, 3 and 4 months  PCV13 in right leg at 2, 4and 12 months | DTaP-IPV-Hib in left leg at 2 months and in right leg at 3 and 4 months*  PCV13 in left leg at 2 months, right leg at 4 months and left arm at 12 months |

## * DTaP-IPV-Hib given in same limb at 3 and 4 months to maintain consistency of co-administration of vaccines in the same limb (i.e. MenC-CRM197 or MenC-TT always given by itself and DTaP-IPV-Hib co-administered with PCV13 at 2 and 4 months – see Appendix A).

## 6.2 Primary and Secondary Endpoints/Outcome Measures

Primary endpoint

The difference in the MenC rSBA GMTs between the participants primed with two doses of MenC-CRM197 (Two Dose MenC Group) and with one dose of MenC-CRM197 (Single Dose MenC-CRM197 Group), one month following the Hib-MenC booster dose at 12 months.

Secondary endpoints

*Reduced MenC component*

After administration of the Hib-MenC booster dose at 12 months of age the following comparisons would be performed in order to assess differences between the:

1) MenC rSBA GMTs between the Two Dose MenC Group and the Control group at 6 and 28 days and 12 months later

2) MenC rSBA GMTs between the Single dose MenC-CRM197 group and the Control group at 6 and 28 days and 12 months later

3) MenC rSBA GMTs between the Single Dose MenC-TT group and the Control group at 6 and 28 days and 12 months later

4) MenC rSBA GMTs between the Single Dose MenC-CRM197 group and the Single Dose MenC-TT group at 6 and 28 days and 12 months later

5) Percentage of participants with MenC rSBA ≥1:8 and ≥1:128 between the Two Dose MenC group and the Control group at 6 and 28 days and 12 months later

6) Percentage of participants with MenC rSBA ≥1:8 and ≥1:128 between the Single dose MenC-CRM197 group and the Control group, at 6 and 28 days and 12 months later

7) Percentage of participants with MenC rSBA ≥1:8 and ≥1:128 between the Single dose MenC-TT group and the Control group, at 6 and 28 days and 12 months later

8) Percentage of participants with MenC rSBA ≥1:8 and ≥1:128 between the Single Dose MenC-TT group and the Control group at 6 and 28 days and 12 months later (Group 4 vs Group 3)

9) Percentage of participants with MenC rSBA ≥1:8 and ≥1:128 between the Single Dose MenC-CRM197 group and the Single Dose MenC-TT group at 6 and 28 days and 12 months later

10) Percentage of participants with MenC rSBA GMTs >1000 between the Two Dose MenC Group and the Control Group, at 6 and 28 days and 12 months later.

11) Percentage of participants with MenC rSBA GMTs >1000 between the Single Dose MenC-CRM197 Group and the Control Group, at 6 and 28 days and 12 months later.

12) Percentage of participants with MenC rSBA GMTs >1000 between the Two Dose MenC Group and the Single Dose MenC-CRM197 Group, at 6 and 28 days and 12 months later.

13) Percentage of participants with MenC rSBA GMTs >1000 between the Single Dose MenC-TT group and the Control group at 6 and 28 days and 12 months later (Group 4 vs Group 3)

14) Percentage of participants with MenC rSBA GMTs >1000 between the Single Dose MenC-TT Group and the Control Group, at 6 and 28 days and 12 months later.

After administration of the last MenC-CRM197 dose at 4 months of age the following comparisons would be performed to assess differences between:

15) MenC rSBA GMTs between the Two Dose MenC Group vs Single Dose MenC-CRM197 Group, Two Dose MenC Group vs Control Group, Single Dose MenC-CRM197 vs Control Group, Single Dose MenC-TT vs Control group, and Single Dose MenC-CRM197 Group vs Single Dose MenC-TT group at 5 and 12 months of age.

16) Percentage of participants with MenC rSBA ≥1:8 between the Two Dose MenC Group vs Single Dose MenC-CRM197 Group, Two Dose MenC Group vs Control Group, Single Dose MenC-CRM197 vs Control Group, Single Dose MenC-TT vs Control Group, Single Dose MenC-CRM197 Group vs Single Dose MenC-TT Group at 5 and 12 months of age.

17) Percentage of participants with MenC rSBA ≥1:128 between the Two Dose MenC Group vs Single Dose MenC-CRM197 Group, Two Dose MenC Group vs Control Group, Single Dose MenC-CRM197 vs Control Group, Single Dose MenC-TT vs Control Group, Single Dose MenC-CRM197 Group vs Single Dose MenC-TT group at 5 and 12 months of age.

18) Number of MenC memory B cells at 5 months, 12 months, 12 months+6 days, 13 months and 24 months (on a subset of participants) between the Two Dose MenC Group vs Single Dose MenC-CRM197 Group, Two Dose MenC Group vs Control Group, Single Dose MenC-CRM197 vs Control Group, Single Dose MenC-TT vs Control Group, Single Dose MenC-CRM197 Group vs Single Dose MenC-TT.

Alternating limb component

After administration of the DTaP-IPV-Hib and PCV-13 the following comparisons would be performed to assess differences between the:

1. Anti-*S. pneumoniae* IgG GMCs or percentage of infants with serum concentration of *S. pneumonia*e specific IgG ≥0.35 g/ml for each of the 13 serotypes at 5, 12, 13 and 24 months of age in children receiving PCV13 in a consistent limb (sub groups ‘a’) vs those receiving this in alternating limbs (subgroups ‘b’).
2. Serotype specific pneumococcal B cell phenotype in a subset of participants at 5, 12, 13 and 24 months of age in children receiving PCV13 in a consistent limb (sub groups ‘a’) vs those receiving this in alternating limbs (subgroups ‘b’).

3. Anti-PRP IgG GMCs or percentage of infants with serum concentration of anti-PRP IgG ≥ 0.15 g/mL and ≥1.0 g/ml at 5, 12, 13 and 24 months of age in children receiving DTaP-IPV-Hib in a consistent limb (sub groups ‘a’) vs those receiving this in alternating limbs (subgroups ‘b’).

4. Anti-tetanus toxoid GMCs or percentage of participants with anti-tetanus toxoid >0.1IU/ml at 5, 12, 13 and 24 months of age in participants in receiving DTaP-IPV-Hib in a consistent limb (sub groups ‘a’) vs those receiving this in alternating limbs (subgroups ‘b’).

*Reactogenicity*

The following comparisons would be performed to assess differences between:

Local adverse events

1. The percentage of infants with each type of adverse event, and at least one adverse event for local adverse events after one dose of MenC-CRM197 at 3 months (Single Dose MenC-CRM197 Group) vs the second dose of MenC-CRM197 at 4 months (Two Dose MenC Group).
2. The percentage of infants with each type of adverse event, and at least one adverse event for local adverse events after one dose of MenC-CRM197 at 3 months (Single Dose MenC-CRM197 Group) vs one dose of MenC-TT at 3 months (Single Dose MenC-TT Group).
3. The percentage of infants with each type of adverse event, and at least one adverse event for local adverse events after each dose of DTaP-IPV-Hib (at 2, 3 and 4 months) and PCV13 (at 2 and 4 months) in the consistent limb group (sub groups ‘a’) vs. the alternating limb group (subgroups ‘b’).
4. The percentage of infants with each type of adverse event, and at least one adverse event for local adverse events after the 12 month booster MenC and PCV13 vaccination in the
   1. Two Dose MenC Group vs 0 Dose Control Group
   2. Single Dose MenC-CRM197 Group vs. 0 Dose Control Group
   3. Single Dose MenC-TT Group vs. 0 Dose Control Group
   4. Single Dose MenC-CRM197 Group vs. Two Dose MenC Group
   5. Single Dose MenC-CRM197 Group vs Single Dose MenC-TT Group
   6. the consistent limb group vs. the alternating limb group

Systemic adverse events

1. The percentage of infants with each type of adverse event, and at least one adverse event for systemic adverse events after MenC (3 and 4 months), DTaP-IPV-Hib (2,3 and 4 months) and PCV13 (2 and 4 months) vaccination in the:
   1. Two Dose MenC Group vs. 0 Dose Control Group
   2. Single Dose MenC-CRM197 Group vs. 0 Dose Control Group
   3. Single Dose MenC-TT Group vs. 0 Dose Control Group
   4. Single Dose MenC-CRM197 Group vs. Two Dose MenC Group
   5. Single Dose MenC-CRM197 Group vs Single Dose MenC-TT Group
   6. The consistent limb group vs. the alternating limb group
2. The percentage of infants with each type of adverse event, and at least one adverse event for systemic adverse events after the 12 month booster MenC and PCV13 vaccination in the:
   1. Two dose MenC Group vs. 0 dose control Group
   2. Single Dose MenC-CRM197 Group vs. 0 Dose Control Group
   3. Single Dose MenC-TT Group vs. 0 Dose Control Group
   4. Single Dose MenC-CRM197 Group vs. Two Dose MenC Group
   5. Single Dose MenC-CRM197 Group vs Single Dose MenC-TT Group
   6. The consistent limb group vs. the alternating limb group

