### 6.4.4 Randomisation and Code-breaking

Randomisation for all UK and Maltese participants will take place at the Oxford Vaccine Group in the UK on a 10:10:7:4 basis to the four study groups (Two Dose MenC, Single Dose MenC-CRM197, Single Dose MenC-TT and Control Group). Each study group would then be randomised on a 1:1 basis to the consistent or alternate limb subgroup (a and b). 64 children from each of the Two Dose MenC, Single Dose MenC-CRM197 and Single Dose MenC-TT groups will also be randomly selected, as well as all the children in the Control group, to have the 12 month + 6 day blood visit, . Randomisation will occur by means of opening in a sequential manner a sealed envelope containing the study group the child is to be randomised to. These envelopes will be prepared by the study statistician and the list held by the statistician and the study sites.

Due to the nature of the study, the study is unblinded, therefore no unblinding procedure is required. Analysis of immunogenicity and safety data will be performed by study staff and laboratory staff in linked-anonymised form such that lab samples and diary cards will only be labelled with participant initials/number. In the event of twins being enrolled from the same family, the diary card may be labelled with the participant’s first initial or name.

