**Local adverse events**

1. percentage of infants with each type of adverse event, and at least one local adverse event after each dose of MenC vaccine (at 3 and 4 months)
   1. Single dose MenC-CRM197 Group vs. Two dose MenC Group
   2. Single Dose MenC-CRM197 Group vs Single Dose MenC-TT Group
2. percentage of infants with each type of adverse event, and at least one local adverse event after each dose of DTaP-IPV-Hib (at 2, 3 and 4 months) and PCV13 (at 2 and 4 months)
   1. the consistent limb group vs. the alternating limb group
3. percentage of infants with each type of adverse event, and at least one local adverse event after the 12 month booster Hib-MenC and PCV13 vaccination
   1. Two dose MenC Group vs. 0 dose control Group
   2. Single dose MenC-CRM197 Group vs. 0 dose control Group
   3. Single dose MenC-CRM197 Group vs. Two dose MenC Group
   4. Single dose MenC-TT Group vs 0 dose control Group
   5. Single dose MenC-CRM197 Group vs Single dose MenC-TT Group
   6. the consistent limb group vs. the alternating limb group

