## 9.2 The Number of Participants

This is a non-inferiority trial assessing whether there is any difference in the antibody level between infants who receive no priming doses of MenC and those who receive 1 priming dose or 2 priming doses of MenC-CRM197.

The total sample size for the study is 498 participants randomised on a 10:10:7:4 basis to the 4 study groups. This will result in 160 participants in the Two Dose MenC group, 160 in the Single Dose MenC-CRM197 group, 114 in the Single Dose MenC-TT group, and 64 in 0 dose MenC (Control) group. Based on a mean (SD) log SBA of 3.47 (0.9) at 1 month after booster for 2 dose MenC12, 160 participants per group are required for the comparison between the Single Dose MenC-CRM197 and the Two dose MenC groups to detect 10% non-inferiority with a 2.5% level of significance (1-sided), 90% power and allowing for a 12.5% drop-out rate. An additional 114 participants will be required for the Single Dose MenC-TT group to allow a comparison with the Single Dose MenC-CRM197 primed group, allowing for a 12.5% drop-out rate.

No sample size calculation for the alternate limb component of the trial is included as the data generated here will be pilot data.

| Non-inferiority margi | Estimated difference | Power | Sample size required per group | Total sample size required |
| --- | --- | --- | --- | --- |
| 5% | -0.18 | 90% | 526 | 1052 |
|  |  | 80% | 393 | 786 |
| 7.5% | -0.26 | 90% | 253 | 506 |
|  |  | 80% | 190 | 380 |
| **10%** | **-0.35** | **90%** | **140*** | **280** |
|  |  | 80% | 105 | 210 |

** Requires 160 participants per group when allowing for a ‘dropout’ rate of 12.5%*

A previous study has shown the mean (SD) logSBA=2.85 (0.48) at 1 month following a 12 month dose of MenC vaccine with no prior MenC immmunisation43. Making the reasonable assumption that the SBA titres are relatively stable in the one month period after the vaccination, these statistics were used to calculate a sample size for a comparison between the one dose group and 0 dose control group at 6 days after the 12 month vaccination.

To detect a difference of 0.285 (10% of 2.85) between groups of equal size of 56 with a significance level of 0.05 (2-sided), would provide a power of 88%. Allowing for 12.5% drop outs, the initial size of 0 dose control group should be 64 infants. This therefore enables the 6 day blood test to be performed on only a subset of participants (64) in each of the other groups.

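### The 3-month reactogenicity comparison of MenC-CRM197 with MenC-TT uses only the Single Dose MenC-CRM197 group, although the Two Dose group has been treated identically up to that visit; pooling would narrow the interval by about 11%

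*Protocol*

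**What the plan says.** Section 6.2, Reactogenicity, local item 2, compares local events "after one dose of MenC-CRM197 at 3 months (Single Dose MenC-CRM197 Group) vs one dose of MenC-TT at 3 months (Single Dose MenC-TT Group"). Section 9.1 C, local item 1, covers "at least one local adverse event after each dose of MenC vaccine (at 3 and 4 months") and names as its second comparison "Single Dose MenC-CRM197 Group vs Single Dose MenC-TT Group". The same pair is the fifth comparison under systemic item 1 in both 6.2 and 9.1 C, where the item spans the 2-, 3- and 4-month vaccinations.

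On treatment, section 6.1 says: "Participants would be randomised to receive MenC-CRM197 at 3 and 4 months (Two Dose MenC Group), or a single dose at 3 months". The other infant vaccines are common to every group: "All participants will receive the DTaP-IPV-Hib vaccine at 2, 3 and 4 months and the PCV13 at 2 and 4 months". Section 9.2 gives the group sizes: "160 participants in the Two Dose MenC group, 160 in the Single Dose MenC-CRM197 group, 114 in the Single Dose MenC-TT group", with 64 in the Control group.

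In 6.2, the infant MenC doses of the Two Dose group enter the local comparisons only through local item 1, where Single Dose MenC-CRM197 is set against a later dose: "vs the second dose of MenC-CRM197 at 4 months (Two Dose MenC Group").

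**The concern.** At the 3-month visit two randomised groups receive a first dose of MenC-CRM197 and one receives a first dose of MenC-TT. The question for that visit is how reactions to the two vaccines differ, and both MenC-CRM197 groups can answer it. The plan draws on one of them.

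Reactions to each dose of these vaccines are a stated secondary objective (reduced dose MenC component, objective 8), and the sample size was not set for any reactogenicity comparison. Precision here is therefore whatever the group sizes happen to give, and some of it is forgone without a stated reason. What is at stake is the width of the interval for a secondary safety contrast. Its validity and the primary non-inferiority analysis are not in question.

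**Working it through.** **Are the two MenC-CRM197 groups the same up to that visit?** Appendix A, within each limb subgroup:

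| | Two Dose (Group 2) | Single Dose MenC-CRM197 (Group 1) |
| --- | --- | --- |
| Visit 1, a | DTaP-IPV-Hib + PCV13, right | the same |
| Visit 1, b | DTaP-IPV-Hib + PCV13, left | the same |
| Visit 2, a and b | DTaP-IPV-Hib right, MenC-CRM197 left | the same |
| Visit 3 | MenC-CRM197 given | no MenC vaccine |

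They first differ at Visit 3 (4 months). Limb is randomised 1:1 within each study group (6.4.4), so it is balanced between them. The 4-day diary card is issued at Visit 2 with no group excepted (6.3.6), so the data will exist.

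**Where do the Two Dose group's 3-month data go?** In no reactogenicity list of 6.2 or 9.1 C is the group compared with MenC-TT. In 9.1 C, local item 1, it appears against Single Dose MenC-CRM197; at 3 months that compares identical vaccines.

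**Group sizes.** The plan gives no power for reactogenicity, so the only figures of its own to reproduce are the group sizes.
- Non-inferiority with margin 0.35, SD 0.9, one-sided 2.5% and 90% power: 2 × (1.96 + 1.2816)² × 0.9² / 0.35² = 139 per group (plan: 140).
- With 12.5% dropout: 140 / 0.875 = 160, as stated.
- Allocation "on a 10:10:7:4 basis to the four study groups": 498 × 10/31 = 160.6, 498 × 7/31 = 112.5 and 498 × 4/31 = 64.3 (plan: 160, 114 and 64).

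**Precision.** For a common event rate, the variance of a risk difference is proportional to 1/n(CRM197) + 1/n(TT).
- As planned: 1/160 + 1/114 = 0.01502
- Pooled: 1/320 + 1/114 = 0.01190
- Variance ratio: 0.792, so 21% lower
- Standard-error ratio: √0.792 = 0.890, so the interval is 11% narrower

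With 12.5% loss (140, 280 and 100 infants) the standard-error ratio is again 0.890. The gain stops at 11% because the 114 MenC-TT infants become the limiting arm.

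**In percentage points.** Half-width of the 95% interval for the risk difference, enrolled numbers, assumed common event rate:

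| Assumed rate | 160 v 114 | 320 v 114 |
| --- | --- | --- |
| 10% | 7.2 | 6.4 |
| 30% | 11.0 | 9.8 |
| 50% | 12.0 | 10.7 |

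**Power, under assumed rates only.** The protocol gives no event rates. Unadjusted two-proportion comparison, two-sided 5%, enrolled numbers:

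| Assumed rates, CRM197 v TT | 160 v 114 | 320 v 114 |
| --- | --- | --- |
| 10% v 20% | 64% | 76% |
| 20% v 35% | 79% | 88% |
| 30% v 45% | 72% | 82% |
| 50% v 65% | 70% | 80% |

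With the direction reversed, the first row becomes 61% to 70%.

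**Systemic events against Control.** Section 6.2 and 9.1 C already list Two Dose v Control and Single Dose MenC-CRM197 v Control separately. Combining them for 3-month events would give √[(1/320 + 1/64) / (1/160 + 1/64)] = √(0.01875 / 0.02188) = 0.926, an interval about 7% narrower.

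**The case against.** The strongest reply is that nothing in the plan is false. Group 1 v Group 4 is a valid randomised comparison, it follows the design (section 9.2 adds the MenC-TT group for comparison with the Single Dose MenC-CRM197 group), and no power was claimed for it. All of that stands. It limits the point to efficiency but does not remove it, because the protocol itself fixes this pair and a more precise contrast is available from the same diary cards.

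A second reply has some substance. The trial is unblinded and parents record the reactions. Parents in Groups 1 and 4 both expect one infant MenC dose, whereas parents in Group 2 expect two. The planned contrast holds that expectation constant and the pooled one does not quite. The effect is probably small, but it is a reason to show both contrasts and not to claim that pooling is free of any possible bias.

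Two stronger readings are tempting and the documents do not support them. A reader might infer that half of the MenC-CRM197 reactogenicity data go unused. That is true of this contrast alone: section 9.1 C tabulates events for every dose group after each vaccination, and the Two Dose group also informs the centre and limb terms of the model. A reader might also infer that the Two Dose group is missing from the systemic comparison with Control. It is not, since it has its own contrast there.

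**Conclusion.** The point holds as a modest loss of precision in a secondary safety comparison. It applies to the 3-month MenC-CRM197 v MenC-TT contrast for local events (6.2 local item 2; 9.1 C local item 1, second comparison) and to the 3-month part of the same contrast for systemic events (systemic item 1, fifth comparison).

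The firm figures are a 21% lower variance and an 11% narrower interval. They rest on the planned group sizes, roughly equal loss across groups and similar event rates in the two arms. The power gains are illustrations, because the event rates are assumed and the planned model adjusts for limb and centre. Pooling against Control is optional: no group is omitted there, and the gain is about 7% for 3-month events only.

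**What to change.** In section 6.2 (local item 2 and systemic item 1) and section 9.1 C, state that for local and systemic events after the 3-month visit, MenC-TT is compared with Groups 1 and 2 combined. The planned logistic model can supply this as the contrast between Group 4 and the equally weighted average of the Group 1 and Group 2 terms, or by recoding the factor for that visit to the MenC vaccine received. Report the Group 1-only contrast beside it as a check on open-label reporting. Keep the groups separate from the 4-month visit onward. Say that the Single Dose v Two Dose comparison at 3 months is of identical vaccines, so that it is not at odds with the pooling.

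The cost is a few sentences, with no added infants, visits or assays. The downside is that systemic item 1, which spans several visits, must be split by visit for this contrast. The same split would be needed if the optional pooling against Control were adopted.
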